### Exclusion Criteria:

Organic or pseudo-obstruction, primary eating or swallowing disorders, positive pregnancy test result, psychogenic vomiting, peritoneal dialysis, drug dependent, morbid obesity, active malignancy and whoever received PP or GES in the past.

**D2) Sample Size:** As this study is designed to conclude that pyloroplasty is not inferior to GES plus pyloroplasty, the sample size for the non-inferiority trial by including % normalization of the GE as the binary outcome is calculated based on: "Blackwelder WC."Proving the Null Hypothesis" in Clinical Trials. Control. Clin. Trials 1982; 3:345-353." GE was normalized in 60 % of GP patients with GES-ON

plus Pyloroplasty based on our preliminary data. On the other hand, based on our patients' database, GES alone normalizes GE in around 18% of GP patients, predominantly in idiopathic GP. By defining non-inferiority limit equal to  $(60 - 18 = 42\%)$ , and percentage of success in the GES-ON plus pyloroplasty group, 17 patients will be included in each arm of this study. Therefore, this study is designed to include overall 34 drug-refractory GP patients who will undergo surgery for GES implantation plus pyloroplasty. Based on our records, we have at least 2 surgeries per month; therefore, we predict that it takes approximately 1.5 years to recruit all patients.

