PAGI-SYM and TSS questionnaires will be filled every 2 weeks during the study period. GES implantation together with the Heineke-Mikulicz PP will be performed laparoscopically (<10% of cases may require open approach). Only one surgeon using the same technique at all times will perform the surgeries. In GES-ON group, GES will be turned on immediately after the operation. On the other hand, in GES-OFF group, the GES will remain OFF for the first 3 months, while symptoms will be recorded again in both groups. After 3 months, follow up GET will be performed and in GES-OFF group, the device will be turned ON. Both groups will be followed for 3 more months clinically, to record any possible changes in their symptoms. Moreover, 36-Item Short Form Health Survey (SF-36), Beck depression inventory (BDI), State-trait anxiety inventory (STAI) and the patient health questionnaire (PHQ-15) will be completed at baseline followed by 3 and 6 months after the surgery. The amount of anti-emetics and prokinetics, days of hospitalization and ED visits and any possible complication will be recorded during the study period. Glucose control in diabetic patients will be monitored by HbA1c. Pain will also be monitored regarding narcotic need. During the follow-up patients will be instructed to remain on a mechanical soft diet of smaller meals, low fat, and low fiber. Evaluators of clinical outcome, the radiologist and the biostatistics consultant as well as the patient will remain blind to the GES-ON or -OFF status before the results get finalized. The individual programming the device will have no clinical rule to avoid any bias.

One of our Investigators, [name] is assigned to serve as an un-blind person, who is going to generate a master list of participants by dividing them into two groups based on their etiologies (diabetic or idiopathic). All efforts would be to include similar numbers of idiopathic and diabetic patients in each intervention group based on a block randomization method, allowing for GES to be turned ON at the surgery, or it will stay OFF for the 3-month-long blind portion of the study.

The following flow-diagram summarizes the steps of this study:

[figure not shown]

Early termination of the study will occur if a patient decides not to continue the study or if in the GES-OFF group, the nausea/vomiting symptoms are not manageable after 6 weeks of the operation, which is the usual time for surgical healing.

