- 5) Associations between changes in TSS and ICC count/pyloric fibrosis.
- 6) SF-36, BDI, STAI and PHQ-15 scores and HBA1c (in diabetics) and their association with the treatment as well as gastric emptying/pathological findings.

The normal distribution of the data will be tested based on D'Agostino-Pearson omnibus test, were normality indicates parametric tests. The numerical variables will be reported as means (SD) or Median (Range) at baseline and follow-up visits and will be compared either by appropriate parametric or nan- parametric tests including t-test analysis or Mann–Whitney U test. The time-trends will be analyzed by either Repeated-Measure ANOVA or non-parametric Friedman Test followed by appropriate Post Hoc. Associations will be assessed based on Pearson correlation or Spearman's rho analysis. Data will be presented as bar graphs, time-trend graphs or scatter-plots and tables.

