#### **Amendment to the Protocol #2 Version 11-20-2018**

This amendment is generated to incorporate the following statements criteria and clarifications related to this protocol:

1. Research personnel will contact patients throughout the duration of the project in order to answer any clinical and research-related questions. This may be unscheduled phone calls/ or conversations during visits.
2. Once patients have completed the study period of approximately 6 months, follow-ups will continue to occur under the Humanitarian Device Exemption (HDE) - Study E09056. These clinic follow-up visits will be conducted as they are described under HDE protocol and will take place as long as the subject has the system, in order to ensure the safety and feasibility of such therapy, which could last up to 10 years.

- 317 3. Due to the fact many subjects are from out of town the complication of having the follow-up  
318 appointments fall exactly at 3 and 6 months will be inevitably missed by many. Therefore we  
319 would like to include  $\pm$  6 weeks grace period in order to obtain the follow-up symptom  
320 information within a window of time adequate for all subjects enrolled.  
321
- 322 4. We would like to increase the upper limit of age of patients who could be recruited and  
323 enrolled in this study. Therefore we are changing the age 65 to the age of 70 based on a  
324 statement provided by the manufacturer which is already mentioned in this study-specific  
325 consent form. *"Safety and Effectiveness of this system have not been established for patients*  
326 *under the age of 18 and over the age of 70"*.  
327
- 328 5. We would like to exclude the Beck Depression Inventory (BDI) and State-trait Anxiety  
329 Inventory (STAI) instruments from the list of questionnaires/ assessments included originally  
330 in the protocol. As from the beginning, we are aware that they are very expensive and not  
331 relevant for this study. Those questionnaires were never submitted for IRB approval and were  
332 never obtained any answers from participating subjects.  
333
- 334 6. We are including the following statement into the protocol:  
335 "Due to the fact that many of our participants are diabetics and they are diagnosed with  
336 retinopathy possible legal blindness, or they have tremor/shakes created by certain drugs  
337 (Reglan), they are unable to read questions, and provide numbers or circle proper responses.  

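### The time-trend tests named in D4 (repeated-measures ANOVA or Friedman) suit 2-weekly symptom scores in 34 patients poorly: both need complete rows, and Friedman cannot compare the arms' trajectories

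*Protocol*

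**What the plan says.** All references are to the protocol.

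- **Method (D4, Statistical analysis).** "The time-trends will be analyzed by either Repeated-Measure ANOVA or non-parametric Friedman Test followed by appropriate Post Hoc". The branch is chosen by a normality test: "The normal distribution of the data will be tested based on D'Agostino-Pearson omnibus test, were normality indicates parametric tests".
- **Comparisons at visits (D4, the sentence just before).** Numerical variables at baseline and follow-up "will be compared either by appropriate parametric or nan- parametric tests including t-test analysis or Mann–Whitney U test".
- **Data (D3, Study Design).** "PAGI-SYM and TSS questionnaires will be filled every 2 weeks during the study period". After the 3-month blinded period the GES-OFF devices are switched on, and "Both groups will be followed for 3 more months clinically, to record any possible changes in their symptoms".
- **Size (D2, Sample Size).** "17 patients will be included in each arm of this study", 34 in all. The calculation uses normalisation of gastric emptying, not TSS.
- **Early end of the blind phase (D3; Amendment #2, item 8).** In the GES-OFF group the blind phase may stop if nausea and vomiting are unmanageable after 6 weeks. The amendment adds that this shortens only the blinded phase and that the patient stays in follow-up.

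D4 does not say which time points enter the time-trend analysis, and it names no arm-by-time term.

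**The concern.** Aim 1 concerns TSS with the stimulator ON and OFF, and the 2-weekly forms are the richest data on it. The two named tests use such data badly, for three reasons.

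1. **Complete rows.** Classical repeated-measures ANOVA and Friedman's test use only patients with a value at every occasion. With many occasions and 34 patients, a modest miss rate can remove a sizeable share of the sample.
2. **No arm in Friedman.** The test ranks occasions within each patient. A difference between arms cannot enter the statistic, and running it separately in each arm gives two within-arm p-values but no comparison. This branch may well be reached. In Table 1 (section C1) every one of the seven post-operative symptom means has an SD at least as large as the mean, for example vomiting 0.6 (1.0), on a scale that cannot fall below 0. That suggests skewed items, although the summed TSS may be less skewed.
3. **Selective exclusion.** A GES-OFF patient whose blind phase ends early has no later blinded OFF values. A complete-row analysis of the blind phase drops that patient because of poor symptom control. This would tend to flatter the OFF arm, in a trial meant to show that pyloroplasty alone is not inferior.

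**Working it through.** **The plan's own figure.** D2 gives 17 per arm, from 60% success in both arms and a margin of 60 − 18 = 42 percentage points. Alpha and power are not stated. With one-sided alpha 0.05 and 80% power (inferred):

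n = 2 × 0.60 × 0.40 × (1.645 + 0.842)² / 0.42² = 0.48 × 6.19 / 0.1764 = 16.8, so 17 per arm.

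The figure reproduces. It concerns gastric emptying and has no bearing on the time-trend tests, except that it fixes 34 patients.

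**Number of forms.** One form every 2 weeks gives about 6 in the 3-month blind phase and 12 to 13 over 6 months. I use 6 and 12.

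**Complete rows, independent misses.** The protocol states no miss rate, so m per form is an assumption, and baseline is taken as present for all. Share complete = (1 − m)^K; expected patients = 34 × (1 − m)^K.

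| m (assumed) | K = 2 (3- and 6-month visits only) | K = 6 (blind phase) | K = 12 (6 months) |
|---|---|---|---|
| 2% | 32.7 | 30.1 | 26.7 |
| 5% | 30.7 | 25.0 | 18.4 |
| 10% | 27.5 | 18.1 | 9.6 |
| 20% | 21.8 | 8.9 | 2.3 |

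For example, 34 × 0.9^6 = 34 × 0.531 = 18.1.

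**Complete rows, misses clustered within patients.** Under a beta-binomial with mean m and correlation ρ, share complete = B(a, b + K) / B(a, b), where a = m(1 − ρ)/ρ and b = (1 − m)(1 − ρ)/ρ.

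| ρ | m | K = 6 | K = 12 |
|---|---|---|---|
| 0.2 | 5% | 27.8 | 25.2 |
| 0.2 | 10% | 22.5 | 18.4 |
| 0.5 | 5% | 30.0 | 29.1 |
| 0.5 | 10% | 26.4 | 24.7 |

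Over 12 forms at 5% to 10% missing, the loss is therefore 46% to 72% of patients under independence, and 14% to 27% with strong clustering (ρ = 0.5).

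**Does Friedman respond to the arm?** Simulation with 17 patients per arm, 7 occasions, normal errors with SD 1, a patient effect with SD 1, and 2,000 runs:

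- Constant difference of 3 error SDs between arms, no time effect: Friedman rejected in 5.8% of runs, about its nominal 5%. Mann-Whitney at the last occasion rejected in 100%.
- Opposite trends of 0.3 SD per occasion, so the arms end 2 × 0.3 × 6 = 3.6 SDs apart: pooled Friedman rejected in 0.9%.

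Friedman is blind to the randomised contrast whatever the amount of missing data.

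**The case against.** **The randomised comparison is not lost overall.** A reader might infer that on the non-parametric branch ON and OFF are no longer compared at all. D4 does not support this. The preceding sentence plans t-test or Mann-Whitney comparisons, and repeated-measures ANOVA can carry arm and arm-by-time if set up as a mixed-design model. Within-group change is also a legitimate target under Aim 3. What is missing is only the between-arm test of the trajectory under Friedman. This objection stands.

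**The size of the loss is not established.** A reader might also infer that most of the trajectory data would be discarded, pointing to item 3 of Amendment #2, which begins "Due to the fact many subjects are from out of town" and expects many missed appointments. That item concerns visits falling exactly at 3 and 6 months, and it adds a window of 6 weeks either side so that the symptom data are still obtained. Items 6 and 7 allow help with completing forms and assessment by phone. No rate of missed forms is given, misses often cluster, and D4 does not say that every 2-weekly form enters the test or that one trend is fitted across all 6 months. This objection stands too, so the figures above are scenarios.

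**Detail belongs in the SAP.** Missing-data rules, covariance and model terms are commonly left there, and their absence is no finding. But D4 does not leave the method open. It names two tests, and that stated choice is the point.

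**It is secondary.** The sample size rests on gastric emptying. This is accepted and is reflected in the weight given.

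**Conclusion.** The point holds as a weakness in a stated secondary method.

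Two parts need no assumption about missing data. Classical repeated-measures ANOVA and Friedman require complete rows, and Friedman gives no ON-versus-OFF test of the trajectory.

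The size of the complete-row loss is conditional. If all 2-weekly forms are used and 5% to 10% are missed independently, 25 to 18 of 34 patients remain over the blind phase and 18 to 10 over 12 forms. With strong clustering, 29 to 25 remain over 12 forms. With only the 3- and 6-month visits, about 31 to 28 remain.

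The selective exclusion of GES-OFF patients whose blind phase ends early follows if blind-phase rows must be complete. How many patients that affects cannot be said from the protocol.

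**What to change.** Replace the time-trend sentence in D4 with a linear mixed model for repeated measures on all available blind-phase TSS values:

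- Terms: arm, time, arm-by-time, baseline TSS and etiology.
- A prespecified, parsimonious covariance (for example AR(1)) with small-sample degrees of freedom (for example Kenward-Roger), given 34 patients.
- Report the ON minus OFF contrast at the end of the blind phase with its confidence interval. Name the week at which it is taken, since Amendment #2 lets the 3-month visit move by up to 6 weeks either way.
- State how values after an early end of the blind phase are handled.
- Analyse months 3 to 6, when both arms are ON, as a separate phase.

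Every patient with a baseline and at least one usable later form then contributes, including those whose blind phase is cut short.

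**Cost.** Wording only; no new data or patients. The covariance structure must be fixed in advance. The model keeps the data recorded before an early end but does not by itself remove bias from informative early ends, so the handling rule is needed as well.

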Additionally, as reported, approximately 40% of GP patients who are refractory to medical therapy and requiring GES therapy have a depletion of antral ICC. Moreover, our recent research has revealed that more than 70% of these patients show depletion of pyloric ICC. Therefore, we would like to assess whether pyloric and antral ICC counts could predict response to pyloroplasty during GES-ON and -OFF periods .

This concept of our study requires patients to sign, the specific IRB-approved consent form for E14018 study in order to provide a tissue sample as it is described under that protocol.

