**Histological evaluation of the biopsy samples:** Paraffin embedded formalin fixed tissues will be cut at 3-4 microns thick and mounted on slides containing paired sections from cases and controls. Subsequently, the tissues will be deparaffinized and immunostained by BenchMark XT automated staining instrument. Briefly, the slides will through peroxidase block and antigen retrieval solutions before applying the primary antibodies (C-Kit clone YR145 from Cellmark, Rocklin, CA). Then, the slides will be washed and incubated with the secondary antibody followed by horseradish peroxidase (HPR). At the end, Chromogen will be added and the slides will be counter-stained by Hematoxylin. Pathology slides will be read by a pathologist who will be blind to the diagnosis of the patients, ICC will be counted per high power field (HPF) and the mean of ICC from examining 20 HPF will be calculated. For collagen fibrosis, the biopsies will be stained with trichome. Presence of diffusely distributed collagen between single muscle fibers will be defined as fibrosis and graded as mild, moderate and severe.

**Gastric emptying test:** Gastric emptying test will be performed utilizing a standardized meal consisting of egg beaters labeled with 99m technetium sulfur colloid accompanied by 2 toasts with strawberry jelly and 120 cc of water will be given to the patients (total calories- 240 and 2% fat). Anterior and posterior images will be obtained in the standing position immediately after meal ingestion and at 30 minutes, 1, 2, 3 and 4 hours. Geometric mean calculation and decay correction will be performed on all images. The radiologist will also be blind to the treatment groups.

The radiation exposure of a gastric emptying is equivalent to a chest x-ray or flying across country on an airline. Therefore, this test can be justified for repeating in 3 months.

**D4) Statistical analysis:** In the current study, the following parameters will be analyzed:

- 1) Changes of total gastroparesis symptom scores (TSS) and gastric retention of the radiolabeled meal (%) at 2-4 hrs in each group. TSS will include both severity and frequency.
- 2) Total Symptom Score (TSS) with severity and frequency of gastroparesis symptoms in each etiological subgroup of patients if enough study power would be achieved.
- 3) Associations between changes in gastric emptying and TSS.
- 4) Associations between changes in gastric emptying and ICC count/ pyloric fibrosis.

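### Section D4 gives treatment arm no role in the emptying, symptom and tissue correlations; adjusting for arm is a minor, low-cost improvement

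*Protocol*

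**What the plan says.** Section D4 (Statistical analysis) lists three associations without mentioning arm:

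- item 3: "Associations between changes in gastric emptying and TSS";
- item 4: "Associations between changes in gastric emptying and ICC count/ pyloric fibrosis";
- item 5: "Associations between changes in TSS and ICC count/pyloric fibrosis".

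The method follows in the same section: "Associations will be assessed based on Pearson correlation or" Spearman's rho. No adjustment, stratification or interaction is named for these items. Elsewhere the list does name a grouping. Item 1 concerns TSS change and "gastric retention of the radiolabeled meal (%) at 2-4 hrs in each group", item 2 refers to etiological subgroups, and item 6 refers to treatment.

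Section B (Background/significance) states the tissue question as wanting to "assess whether pyloric and antral ICC counts could predict response to pyloroplasty during GES-ON and -OFF periods". Under section D3 every patient has a pyloroplasty. The device is switched on at surgery in one arm and left off for the first 3 months in the other, and the follow-up emptying test is at 3 months. Pyloroplasty without active stimulation is therefore seen only in the GES-OFF arm, and only in that first period.

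**The concern.** A simple correlation has no term for the randomised factor. This matters differently for the two kinds of association.

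**Item 3.** Change in GE and change in TSS are both post-randomisation outcomes. Randomisation does not protect a correlation between two outcomes that arm can each shift. In pooled data, the difference between arms can produce a correlation even when the two measures are unrelated among patients within an arm.

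**Items 4 and 5.** The Abstract describes ICC counts as a baseline measure, and I take fibrosis in the same way. Arm is then independent of both in expectation. The difficulty is that an arm shift in the outcome adds variance and weakens the correlation. A pooled estimate also averages patients with pyloroplasty alone and patients with pyloroplasty plus stimulation, whereas section B names the ON and OFF periods.

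At stake are the reading of item 3 and the answer to Specific Aim 4. Neither is the outcome on which the trial is sized.

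**Working it through.** **Plan's own figure.** Only the 17 per arm in section D2 is used here, and it reproduces. With success 60% in both arms, a margin of 60 − 18 = 42 points, one-sided alpha 0.05 and 80% power (alpha and power are not stated in D2, so they are assumed):

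n = (1.645 + 0.842)² × 2 × 0.6 × 0.4 / 0.42² = 6.18 × 0.48 / 0.1764 ≈ 16.8, i.e. 17 per arm, 34 in total.

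**Item 3: correlation produced by arm alone.** Let dG and dT be the arm effects on GE change and TSS change in within-arm SD units, with 1:1 allocation and zero within-arm correlation. Then

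r = (dG·dT/4) / √[(1 + dG²/4)(1 + dT²/4)].

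For example, dG = 0.5 and dT = 1 give 0.125 / √(1.0625 × 1.25) = 0.11; dG = dT = 1 give 0.25 / 1.25 = 0.20. False-positive rates come from 20,000 simulated trials (17 per arm, two-sided 5%):

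| dG | dT | pooled r | pooled rejection | arm-adjusted rejection |
|---|---|---|---|---|
| 0 | 1.0 | 0 | 5.0% | 5.1% |
| 0.2 | 1.0 | 0.04 | 5.8% | 4.9% |
| 0.5 | 1.0 | 0.11 | 9.4% | 5.2% |
| 1.0 | 1.0 | 0.20 | 20.8% | 5.0% |
| 1.5 | 1.5 | 0.36 | 59.5% | 5.0% |

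The protocol gives no arm effect for ON against OFF after pyloroplasty, so every dG and dT is an assumption. The protocol's premise, that stimulation does little or nothing to emptying (Abstract and section B), points to the top rows. If arm moves only one of the two measures, the induced r is zero.

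**Items 4 and 5: dilution.** With the predictor independent of arm, a common within-arm correlation is multiplied by 1/√(1 + dT²/4) when the arms are pooled:

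- dT = 0.5: 0.97
- dT = 1.0: 1/√1.25 = 0.89
- dT = 1.5: 0.80

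For a common correlation of 0.5 and a 1 SD arm shift, simulated power is 78% pooled and 87% adjusted for arm.

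**Precision of a single-arm estimate.** By Fisher's z, the correlation detectable with 80% power at two-sided 5% is tanh[(1.96 + 0.8416)/√(n − 3)]:

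- n = 17: tanh(2.8016/√14) = 0.63
- n = 34: tanh(2.8016/√31) = 0.46

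If the relation is the same in both arms with r = 0.6 and a 1 SD arm shift, using the GES-OFF arm alone gives 76% power, against 97% for the arm-adjusted estimate from all 34.

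**The case against.** **Pooling is not stated.** A reader might infer that the protocol commits to ignoring arm. It does not: D4 names a statistic, not an analysis set, correlations can be run within arm, and section B mentions ON and OFF periods. Covariate detail for secondary analyses may also sit in a statistical analysis plan that is not shown. This stands, so everything above is conditional on pooling. It does not remove the point, because D4 fixes a bivariate method and names a grouping for other items but not for these.

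**The GE-TSS artefact may be negligible.** Both arms have the same pyloroplasty, the protocol expects stimulation to leave emptying largely unchanged, and its stimulation-only cohort (section C2) showed no significant change in mean emptying. A reader might take 21% or 60% as the expected error rate, but the documents do not support arm effects of that size on emptying. The 60% and 18% normalisation rates in D2 correspond to about 1.17 SD on a latent normal scale, but they compare combined treatment with stimulation alone, which is not this trial's contrast. In reply, Specific Aim 2 exists to examine emptying under ON and OFF, so the analysis should not depend on that premise.

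**No false predictor from arm.** A reader might infer that the arm effect could make ICC or fibrosis look predictive. With pre-treatment measures and randomised arms it cannot do so in expectation. Nor do the documents support a scenario where ICC predicts strongly with the device off and not at all with it on.

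**The GES-OFF arm is small.** Relying on 17 patients as the main estimate would lose power if the relation is common to both arms. This stands and limits the remedy.

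**Conclusion.** The point holds as a minor improvement to secondary analyses. D4 assesses items 3 to 5 by simple correlation and does not carry the ON/OFF distinction of section B into them.

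If the arms are pooled, the GE-TSS correlation has a false-positive rate of about 5% under the protocol's premise, 9% at 0.5 SD on GE with 1 SD on TSS, and 21% at 1 SD on both. Adjustment for arm holds it near 5% throughout. For ICC and fibrosis the effect is dilution (about 0.89 times at a 1 SD arm shift) and a mixture of two treatments, not a spurious association.

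These sizes rest on assumed arm effects, normal outcomes, 17 per arm, and tissue measures that reflect the state before stimulation starts.

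**What to change.** In section D4, state for items 3 to 5 that:

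- associations are estimated at the 3-month assessment, before the GES-OFF devices are switched on, with arm as an adjustment (partial Pearson or Spearman correlation, or a linear model with arm);
- estimates are also shown by arm, with the GES-OFF estimate as the descriptive result for pyloroplasty alone;
- any arm-by-predictor term and all arm-specific estimates are exploratory.

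The change is to wording, plus one degree of freedom for arm; no new data are needed. There are two limits. Arm-specific estimates from 17 patients are imprecise, with a detectable correlation of about 0.63 at 80% power. And because every patient has a pyloroplasty, even the GES-OFF estimate cannot separate prediction of response to pyloroplasty from general prognosis.
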